## Abstract

**Background:**

There has been growing clinical awareness in recent years of the long-term physical and psychological consequences of the SARS-CoV-2 virus, known as Long COVID. The prevalence of Long COVID is approximately 10% of those infected by the virus. Long COVID is associated with physical and neuropsychological symptoms, including those related to mental health, psychological wellbeing, and cognition. However, research on psychological interventions is still in its early stages, in which means that available results are still limited. The main objective of this study is to evaluate the effects of a program based on amygdala and insula retraining (AIR) combined with mindfulness training (AIR + Mindfulness) on the improvement of quality of life, psychological well-being, and cognition in patients with Long COVID.

**Methods:**

This study protocol presents a single-blind randomized controlled trial (RCT) that encompasses baseline, post-treatment, and six-month follow-up assessment time points. A total of 100 patients diagnosed with Long COVID by the Spanish National Health Service will be randomly assigned to either AIR + Mindfulness (n = 50) or relaxation intervention (n = 50), the latter as a control group. The primary outcome will be quality of life assessed using the Short Form-36 Health Survey (SF-36). Additional outcomes such as fatigue, pain, anxiety, memory, and sleep quality will also be evaluated. Mixed effects regression models will be used to estimate the effectiveness of the program, and effect size calculations will be made.

**Discussion:**

Long COVID syndrome is a clinical condition characterized by the persistence of symptoms for at least 12 weeks after the onset of COVID-19 that significantly affects people’s quality of life. This will be the first RCT conducted in Spain to apply a psychotherapy program for the management of symptoms derived from Long COVID. Positive results from this RCT may have a significant impact on the clinical context by confirming the beneficial effect of the intervention program being evaluated on improving the symptoms of Long COVID syndrome and aiding the development of better action strategies for these patients.

**Trial registration:**

Clinical Trials.gov NCT05956405. Registered on July 20, 2023.

## Introduction

### Background and rationale

Long COVID, also known as Post-COVID Conditions or SARS-CoV-2 infection with post-acute sequelae, refers to a set of multiple organ symptoms that persist in patients who have experienced SARS-CoV-2 infection, even after the acute phase of the disease [1]. Approximately 10% of individuals experience these symptoms after the resolution of their acute COVID phase [2]. Such symptoms exhibit variability and are multisystemic, and they may be persistent or limited over time. Symptoms consist of fatigue that does not improve with rest, shortness of breath, fever, myalgia, sore throat, chest and back pain, as well as other muscle and mild neuropathic pain. Additionally, symptoms include orthostatic hypotension, intestinal motility issues, symptoms of neural disorders, insomnia that can disrupt sleep and rest, hyperactivation of the sympathetic system, cognitive deficits, anxiety, and the inability to manage stress [3, 4].

Furthermore, it is necessary to acknowledge the psychosocial impact of the miscellaneous symptoms described on the lives of individuals dealing with Long COVID. Limitations in performing everyday activities such as self-care, household tasks, shopping, or engaging in social activities can be constraining, with variation based on symptom severity. Consequently, these limitations generate feelings of isolation and loneliness, which can contribute to secondary depression [5, 6]. All these symptoms can have a significant impact on their physical, occupational, and emotional health, often resulting in social and economic challenges for both individuals and their families [1]. In summary, psychological distress frequently accompanies patients with Long COVID, who often present with symptoms of depression, anxiety, and diminished quality of life, among others [5, 7–10].

Research suggests that Long COVID symptoms are caused by chronic inflammation and immune dysregulation in the body [1]. Recent studies have indicated a potential link between Long COVID and neurological complications, such as cognitive impairment and brain fog [11]. In fact, Long COVID syndrome presents similarly to myalgic encephalomyelitis/chronic fatigue syndrome (ME/CFS) [3], which is characterized by fatigue and immune and cognitive dysfunctions [8]. Due to their similarity, there is reason to believe that ME/CFS treatments could be effective in resolving Long COVID. Emerging evidence suggests that the impact of Long COVID extends beyond physical health, with a significant proportion of patients reporting challenges in their professional and social lives [12]. This underscores the complex nature of the condition and highlights the need for comprehensive treatment approaches and the importance of addressing the holistic wellbeing of individuals affected by this condition.

Psychological approaches, including mind-body therapies such as mindfulness training, have demonstrated their effectiveness for the treatment of these types of pathologies by improving mental health and physical function, while reinforcing acceptance and reducing symptoms [13–15]. Amygdala and insula retraining (AIR) techniques were initially developed for CFS patients as a method to reduce the chronic over-sensitization and heightened fear response of the amygdala, which may underlie certain symptoms associated with both CFS and fibromyalgia [14–16]. These techniques aim to retrain conditioned somatic signaling in the brain that can maintain the nervous and immune systems in a constant state of alert. This retraining is achieved by means of a specialized intervention designed to strengthen neurological inhibitory mechanisms in areas of the prefrontal and orbital cortices, the insula, and the anterior and posterior cingulate [17–20]. AIR techniques involve repetitively interrupting signals from the amygdala and insula using a variety of personalized practices for each patient [18, 20]. In essence, patients learn to recognize internal symptom signals and then take action to disrupt the signaling. Additionally, mindfulness training has been shown to reduce amygdala reactivity and increase gray matter volume in the prefrontal cortex and insula [21]. Consequently, the prospect of combining mindfulness training with AIR techniques to enhance effects is appealing. AIR training has demonstrated efficacy in treating chronic conditions such as ME/CFS [14, 15], and the combined approach of AIR techniques with mindfulness training (AIR + Mindfulness) has proven effective in managing fibromyalgia symptoms [17, 20–22].

However, despite the previously reported positive results, there is still no evidence regarding the possible mediating variables associated with the AIR + Mindfulness program since it is a relatively new psychotherapeutic strategy. Despite this, and based on the results obtained in previous studies, psychological variables such as mindfulness skills, emotion regulation, and experiential avoidance could play a mediating role in the improvement of Long COVID syndrome through the application of the AIR + Mindfulness program [22–24]. For example, a recent observational study identified a relationship suggesting that experiential avoidance is associated with the greater severity of fatigue and pain perceived by patients with COVID-19, and that psychological interventions aimed at working on this psychological variable would favor an improvement in the severity of symptoms in these patients [23]. On the other hand, a longitudinal study that investigated the role of emotion regulation on mental health found that people who used maladaptive emotion regulation strategies reported more symptoms of anxiety, depression, poorer sleep quality, and less life satisfaction [24]. For this reason, psychological interventions aimed at promoting the learning of adaptive regulation strategies (i.e., integrative emotion regulation [25] could be expected to have a positive impact on the improvement and management of symptoms associated with COVID-19 and Long COVID.

Extensive research is being conducted to test pharmaceutical, biological, dietary, homeopathic, and rehabilitative remedies for the treatment of Long COVID symptoms. However, an effective intervention strategy still remains elusive [26, 27]. Recent evidence suggests that psychological interventions can improve mental health and alleviate a variety of symptoms for Long COVID patients [28, 29].

### Objectives and hypotheses

The primary aim of the study proposed in this protocol is to evaluate the impact of the AIR + Mindfulness on enhancing the quality of life of patients with Long COVID. The secondary objectives include (a) to examine the effects of AIR + Mindfulness on pain, pain catastrophizing, fatigue, insomnia, anxiety, depression, and memory symptoms; and (b) to analyze the role of mindfulness skills, emotion regulation, and experiential avoidance as potential mechanisms through which AIR + Mindfulness exerts its effects.

The main hypothesis is that AIR + Mindfulness will be more effective than relaxation therapy for improving quality of life among patients diagnosed with Long COVID at post-treatment. The secondary hypotheses are (a) AIR + Mindfulness will be more effective than relaxation therapy for improving pain, pain catastrophizing, fatigue, insomnia, anxiety, depression, and memory symptoms at post-treatment; (b) improvements in all psychological variables will be sustained at the three-month follow-up; and (c) mindfulness skills, emotion regulation, and experiential avoidance will play a mediating role in the improvement observed in the AIR + Mindfulness experimental group compared to the relaxation therapy control group.

## Methods

### Design

This protocol was developed according to the Standard Protocol Items: Recommendations for Interventional Trials (SPIRIT) [30], and it was listed on the ClinicalTrials.gov register on July 20, 2023 (NCT05956405). We designed a parallel group, single-blind, randomized controlled trial (RCT) with two treatment arms and a three-month follow-up. Evaluation will be made of the effectiveness of AIR + Mindfulness (intervention group) compared to relaxation health and wellness therapy (active control group) in patients with Long COVID. Both interventions are structurally similar, consisting of eight two-hour weekly sessions followed by three monthly two-hour sessions. Both groups will attend online workshops for both the AIR + Mindfulness intervention and relaxation therapy. Both groups will receive support materials online and by email. The Consolidated Standards of Reporting Trials (CONSORT) [31] will be applied.

### Setting and study sample

Potential participants will primarily be recruited through collaboration with the Long COVID Association of Aragon (Spain), and they will be required to meet the following inclusion/exclusion criteria. Inclusion criteria: (a) aged 18 years and over; (b) provision of signed informed consent; (c) diagnosis of Long COVID by primary care physicians. Exclusion criteria: (a) under 18 years of age; (b) any diagnosis of a disease that may affect the central nervous system or other psychiatric diagnoses or acute psychiatric illnesses (e.g., severe range of depression, substance dependence or abuse, history of schizophrenia or other psychotic disorders, eating disorders); (c) any medical, infectious or degenerative disease that may affect mood; presence of delusional ideas; and hallucinations consistent or not with mood and suicide risk.

### Sample size

According to a previous study, when use of the AIR + Mindfulness intervention was compared to a similar active control group (i.e., relaxation therapy) on a sample of fibromyalgia patients, it demonstrated an overall improvement in the severity of the disorder––measured using the Fibromyalgia Impact Questionnaire Revised [32], a tool that evaluates the effect of this condition on a person’s wellbeing and quality of life, considering pain levels, physical functioning, sleep quality, fatigue, mood, and the impact of the condition on daily activities––with a moderate effect size (d = 0.60) at post-intervention [22]. Assuming a similar effect size in terms of quality of life on Long COVID symptomatology at post-intervention, in order to detect this difference with an overall α level of 5% and a statistical power set at 80% in two-tailed tests, 42 patients per group are required. Given that a dropout rate of around 15% of the participants is expected [33], the sample size will be increased until the number of 50 participants is achieved per group at the beginning of the study.

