## Data analysis plan

The distribution of the sociodemographic and clinical variables will be presented by frequencies (percentages), medians (interquartile range, IQR) or means (standard deviations, SD), according to their level of measurement and statistical distribution.

The primary analysis will consist of a comparison between AIR + Mindfulness (intervention arm) and relaxation therapy (control arm) at post-intervention, considering the quality-of-life main outcome (SF-36) as a continuous variable. It will be performed using a repeated measures design on an intention-to-treat (ITT) basis, and a linear mixed effects regression by means of the restricted maximum likelihood (RML) method, controlling for age and sex. The “treatment by time” interaction will be calculated to determine possible differences between the study arms over time. The slope coefficient, representing the adjusted mean difference change, as well as its 95% confidence interval (95% CI), will be calculated. Hedge’s g statistic, as an effect size measure of between-group differences, will be calculated from the raw data. The rule of thumb for effect size interpretation will be 0.20 = small, 0.50 = medium, and 0.80 = large.

Secondary analysis will explore the effects achieved in the primary outcome at three-month follow-up, as well as in the secondary outcomes at post-intervention and at three-month follow-up, following the same analytical approach. Sensitivity analysis will assess the effects of missing data, which will be assumed to be missing at random and replaced by multiple imputations based on chained equations, including the main and secondary outcomes of all the waves––as well as routinely collected sociodemographic data. Other secondary analyses will explore reliable change and clinically significant change in quality-of-life improvements using the Jacobson and Truax method [63]. These classifications will be used to calculate the absolute risk reduction (ARR) and the number needed to treat (NNT); a 95% CI for each NNT will also be calculated. We will use a two-sided test with a 0.05 significance level. No corrections for multiple comparisons will be made for the primary analysis––because only one contrast will be made. Secondary analyses will be corrected for multiple comparisons by adjusting the significance threshold according to the Benjamini-Hochberg procedure [64].

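### The sample-size inputs give 44 or 45 patients per group, not 42; 42 completers give about 78% power in a two-sample comparison, a small optimistic shortfall

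*Protocol article*

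**What the plan says.** The Sample size section of the protocol article takes its effect size from an earlier fibromyalgia trial of the same intervention against relaxation, which reported a benefit "with a moderate effect size (d = 0.60) at post-intervention". It assumes a similar effect on quality of life in Long COVID and sets alpha at 5%. It then states "a statistical power set at 80% in two-tailed tests, 42 patients per group are required".

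Dropout is handled next: "Given that a dropout rate of around 15% of the participants is expected", and so "the sample size will be increased until the number of 50 participants is achieved per group at the beginning of the study".

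Two other places complete the inputs. The Methods paragraph of the Abstract gives equal allocation: "AIR + Mindfulness (n = 50) or relaxation intervention (n = 50". The Data analysis plan applies no multiplicity correction to the primary analysis, "because only one contrast will be made", so the full 5% is available. The Sample size section names no formula, no software and no correlation between baseline and post-treatment scores.

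**The concern.** Effect size, alpha, sidedness, power and allocation ratio are all given, so the required number can be recomputed directly. Both standard formulas give more than 42. The number is presented as what 80% power requires, and the enrolment target of 50 per group is derived from it. If it is too low, the stated power is not met by the calculation the section describes, and the error favours the trial. This is the only sample-size justification in the article.

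**Working it through.** **Inputs.** d = 0.60, two-sided alpha 0.05, power 0.80 and dropout of about 15% (Sample size); 1:1 allocation (Abstract, Methods); no split of alpha (Data analysis plan).

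**Required number, normal approximation.**
n per group = 2 × (z₀.₉₇₅ + z₀.₈₀)² / d² = 2 × (1.960 + 0.8416)² / 0.36 = 43.60, rounded up to **44**.

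**Required number, two-sample t-test (noncentral t).**
n = 44.59, rounded up to **45**.

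**Can 42 be recovered another way?**
- A one-sided test gives 35 (normal) or 36 (t-test), so sidedness does not explain it.
- Rounding of d does not explain it. At d = 0.605, the top of the range that rounds to 0.60, the normal formula gives 2 × 7.849 / 0.366 = 42.9, so 43. The t-test gives 43.9, so 44.
- By t-test, 42 per group corresponds to d of about 0.62 (n = 41.8). By the normal formula it corresponds to 2.8016 / √21 = 0.61.

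**Power at the relevant sizes, d = 0.60, two-sided 5%.** The normal column is Φ(d√(n/2) − 1.960). For n = 42 this is Φ(0.60 × 4.583 − 1.960) = Φ(0.790) = 0.785.

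| Analysed per group | Normal | t-test |
|---|---|---|
| 42 | 78.5% | 77.6% |
| 42.5 (= 50 × 0.85) | 79.0% | 78.0% |
| 43 | 79.4% | 78.5% |
| 44 | 80.4% | 79.5% |
| 45 | 81.2% | 80.4% |
| 50 (no dropout) | 85.1% | 84.4% |

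**Dropout step.** 42 / 0.85 = 49.4, so 50, which matches the article. The same step from 44 gives 51.8, so 52 per group (104 in total). From 45 it gives 52.9, so 53 per group (106 in total).

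**Does the planned model change the answer?** The Data analysis plan specifies a linear mixed model with a treatment-by-time interaction, adjusted for age and sex. Its power depends on the baseline-to-post correlation ρ, which is not given, so the values of ρ below are assumptions. All figures are for 42 per group, d = 0.60 on the post-treatment SD, by t-test.
- If each arm's baseline mean is left free, the interaction behaves like a comparison of change scores, with effective d = 0.60 / √(2(1 − ρ)). Power is 63% at ρ = 0.3, 70% at 0.4, 77.6% at 0.5 and 86% at 0.6. It reaches 80% at about ρ = 0.53.
- If the model adjusted for the baseline score (ANCOVA), effective d would be 0.60 / √(1 − ρ²). Power would be 79.2% at ρ = 0.2, 80.1% at 0.25, 81.3% at 0.3 and 88.1% at 0.5.

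**The case against.** The strongest reply is that this hardly matters. The gap is 2 to 3 patients and at most 2.4 power points. It would close if d were 0.61 or 0.62, and d itself is borrowed from another disease and another questionnaire, so its uncertainty is far larger than 0.02. The formula is not named, so 45 is no more authoritative than 44. All of this stands, and it limits the point to a correction of the statement. It does not make 42 right: a required sample size is rounded up to reach the stated power, and 42 falls short on both formulas.

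A second reply is that the trial enrols 50 per group and not 42. That is true, and with everyone analysed power would be 84% to 85%. A reader might therefore infer from the error that the trial as enrolled has only 78% power. The article does not support that as a flat statement: 78% to 79% holds only if the full 15% is lost and the comparison is an unadjusted two-sample one. Equally, the 84% cannot be used to defend the sentence, because the section itself expects the loss.

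A third reply is that the planned analysis is a repeated-measures model and would recover the missing power. The article gives no basis for this. The sizing claims no such gain, and the treatment-by-time contrast may have more or less power than the simple comparison, depending on a correlation that is not stated.

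**Conclusion.** The figure of 42 per group is wrong for the inputs printed beside it. The requirement is 44 (normal approximation) or 45 (t-test), and 42 completers give 78.5% or 77.6% power. The shortfall is small and on the optimistic side. The dropout arithmetic is correct but inherits the low starting figure.

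This rests on a two-sided, equal-allocation, unadjusted two-sample comparison at d = 0.60, which is the only calculation that the Sample size section describes. A reader might go further and conclude that the trial is materially underpowered or must enrol 104 to 106 patients. The documents do not support that: the gap is about two points under full expected dropout, and true power under the planned mixed model cannot be fixed in either direction without the baseline-to-post correlation.

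**What to change.** Keep 100 patients and restate the sample-size sentence along these lines: *42 completers per group give about 78% power for d = 0.60, or 80% for d of about 0.62 (t-test), at a two-sided 5% level in an unadjusted two-sample comparison.* The allowance for 15% dropout, 50 per group, can then stand as written.

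Do not replace this with a more favourable ANCOVA figure unless the primary model is expressly changed to adjust for the baseline score and the assumed correlation is stated. For the treatment-by-time contrast as now described, such a figure could be much too high: at ρ = 0.3, 81% against 63%.

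The cost is one sentence and a slightly less favourable stated power. Enrolment, alpha and the primary analysis do not change.

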### Recruitment

The recruitment of potential participants will be carried out in collaboration with the Long COVID Association of Aragon. The association will be responsible for disseminating the study through its own communication channels without sharing any member data. This dissemination will include informative sessions during the association’s activities and will provide essential information on the study, in addition to the contact details of the research team for those interested in participating. Patients who express interest via email will receive further information by means of a telephone or video call, through which a member of the research group will explain the primary objective of the study. The evaluation process will also be explained at this time. Evaluation, both for the baseline measurement and subsequent follow-up measurements (immediately after the intervention and three months later), will be conducted online. The survey will be hosted on SurveyMonkey®. Prior to starting the questionnaire, participants will have the opportunity to read the information sheet, informed consent form, as well as the privacy regulations and personal data handling policy of the website. Individuals who meet the inclusion criteria, agree to participate, and complete, sign, and submit the signed informed consent form will gain access to the evaluation and will be permitted to complete the initial assessment. This recruitment process will remain active until the required sample size is achieved.

### Randomization, allocation, and blinding

A research assistant will be responsible for assigning a unique code to each participant and communicating it via email. This research assistant will be the sole person with access to participants’ personal data, along with their respective codes and the group to which they are assigned once the allocation process is completed. This information will be securely stored in a password-protected digital file. A duplicate file will be created on a hard drive to which only the lead researcher will have access. Once the baseline surveys have been completed, subject allocation will be conducted by a different member of the research team, who will not be involved in any other study-related tasks. This allocation will be based on a computer-generated random sequence obtained from a reputable source (https://www.randomizer.org). Participants will be assigned to either of these two groups: (1) AIR + Mindfulness group; (2) Control group based on relaxation therapy. Participants and psychotherapists conducting the interventions will not be blinded to the intervention condition for practical reasons. However, blinding will be maintained during the initial assessment (pre-intervention). Additionally, the research assistant responsible for sharing the assessment survey link will be blinded, as will the expert conducting the statistical analysis.

